**Fig. 2 fig2:**
[figure not shown]
Flowchart 2: Illustration of the study procedure during the vessel-based ischemia testing including the dobutamine/volume challenge

Following diagnostic coronary angiography, a 0.014 inch pressure monitoring angioplasty guidewire (PressureWire™ X Guidewire, Abbott, Chicago, Illinois, United States) will be calibrated and positioned in the distal part of the vessel downstream of the anomalous segment. Next, calculation of resting non-hyperemic pressure ratios (i.e. instantaneous wave-free ratio, resting full cycle ratio and Pd/Pa, all calculated as previously described [38,39]) will be performed. After recording the resting indexes, baseline (i.e. under resting condition) IVUS will be assessed at the site of maximal stenosis (minimal cross-sectional area). IVUS pullback will be conducted at a speed of 0.5 mm/s throughout the suspected lesion. Lesion length, oval-vessel shape and minimal cross-sectional area at rest and during pharmacologic stress will be assessed in the Bern University Hospital Corelab.

Further, FFRadenosine will be assessed during administration of intravenous (i.v.) adenosine (140 μg/kg/min for approximately 2min). FFR will be calculated as the ratio of mean distal (non‐ectopic coronary) pressure to mean aortic pressure and will be considered positive if FFR≤0.80 [40].

Last, dobutamine/volume challenge will be performed by administration of i.v. dobutamine at a rate of 20mcg/kg/min for 2 min, followed by 4 min of i.v. dobutamine at a rate of 40mcg/kg/min. In addition, up to 3 L of saline solution will be administered to counteract cardiac preload reduction and subsequent systemic blood pressure drop by dobutamine. If the maximal heart rate (=220-age) will not be reached after 6 min, 0.5–1 mg of intravenous atropine will be given aiming for the maximum tolerable heart rate. Throughout the stress test, aortic as well as distal coronary artery pressure will be recorded continuously for calculation of FFRdobutamine. At maximal achieved heart rate, the above mentioned IVUS protocol will be repeated for the assessment of the hyperemic values (i.e. evidence of a lateral compression). Afterward, dobutamine will be stopped, and esmolol (10 mg stepwise) will be given to slow down the heart rate.

#### Myocardium-based ischemia testing

2.2.2

Nuclear cardiac imaging modalities (single-photon emission computed tomography (SPECT) or positron emission tomography (PET)) are widely used for risk stratification and for the assessment of myocardial perfusion in coronary artery disease. Owing to their ability to measure perfusion through the accumulation of radioactive tracers in the myocardium, nuclear cardiac imaging techniques provide a robust evaluation of myocardial perfusion and, thus, an independent evaluation of the hemodynamic relevance of the anomaly. Of note, combination with CT allowing the allocation to the corresponding vessel territory is crucial because of the often altered situation in AAOCA [23,41,42].

In the NARCO-trial, all patients will undergo nuclear imaging if there is no contraindication, using PET or SPECT with physical (i.e. bicycle ergometer) stress test or a pharmacologic stress test (dobutamine + atropine) if possible, striving for a maximal stress burden [43].

### Image post-processing

2.3

CFD will be performed with dedicated CFD coronary artery software and with general-purpose CFD models [29]. Dedicated CFD models are based on independent, non-commercially available onsite research software developed to estimate FFR from CCTA (cFFR by Siemens Healthineers) [28]. The software allows to calculation of FFR based on the patient's CCTA images after segmentation of the coronary tree. This dedicated CFD model uses fixed assumptions specific to coronary arteries and a simplified model instead of solving the full Navier-Stokes equation, only requiring the user to perform the segmentation of the coronary artery tree. Further analyses will be performed with the use of general-purpose CFD software (e.g. ANSYS 2022R2, Pennsylvania, USA). Lastly, three-dimensional models of the left and right coronary trees will be generated from coronary CTA images using proprietary, purpose-developed software (Mimics, Materialise, Leuven, Belgium) to segment coronary arteries and determine vessel centerlines.

Data from the invasive assessment will be used to validate results of the CFD analysis. The governing Navier–Stokes equations for the conservation of mass and momentum will be solved with the finite volume method (Fluent 14.5, ANSYS). Mean pressure distal to the interrogated lesion will be obtained from the blood flow simulation in the vessel location matching the invasive FFR measurement based on interpretation of the invasive coronary angiography images recording pressure wire position. Matching will be blinded to the invasive FFR measurement. FFRCT values will then be calculated by dividing the mean pressure distal to the coronary anomalous segment (identical to the invasive position) by the mean aortic pressure [44].

Additionally and as an exploratory analysis, we will create 3D models combined of segmented IVUS images and CCTA images [45,46]. These 3D printings will then be used to perform flow-loop analysis [47].

### Sample size

2.4

Concerning the power analysis, a total sample size of 39 (6 of 39 with abnormal FFR≤0.8) achieves 80 % power (1-beta), with a significance level (alpha) of 0.05 to reject the null hypothesis of an area under the receiver operating characteristic curve less than 0.8 (MedCalc Software Ltd, Ostend, Belgium). The projected allocation ratio (6 of 39) is based on previous literature, that ∼18 % of coronary anomalies are associated with an FFR≤0.80 [[40], [48]]. However, based on rarity of coronary anomalies with associated uncertainites concering the prevalence, we will conservatively include 50 subjects for the primary aim.

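### The 80% power stated for 39 patients does not fit a null AUC of 0.8 at any plausible true AUC; the null was probably misdescribed

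*Protocol article*

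**What the plan says.** The power statement is in section 2.4 (Sample size) of the protocol article. Its design is described as "a total sample size of 39 (6 of 39 with abnormal FFR≤0.8"), and the power claimed for that design is 80% at an alpha of 5%. The purpose of the test is put separately in these words: "to reject the null hypothesis of an area under the receiver operating characteristic curve less than 0.8". The software named is MedCalc. No expected AUC is given, and the test is not described as one- or two-sided.

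On the split between positives and negatives: "The projected allocation ratio (6 of 39) is based on previous literature", which is cited as about 18% of anomalies having FFR≤0.80. Because that prevalence is uncertain, "we will conservatively include 50 subjects for the primary aim". This is the only power statement in the article. It supports the primary aim in section 1.2, a CCTA-based rule-out test judged against invasive FFR under dobutamine.

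**The concern.** A null AUC of 0.8 is a demanding benchmark, and six positives carry little information about an AUC. A power of 80% against that null looks far too high unless the true AUC is close to 1, and the article does not say what AUC was expected.

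The null decides what the trial can claim. If it is 0.8, rejection supports an AUC above 0.8, but the trial will probably not reject even for a good CCTA rule. If it is 0.5, the power is plausible, but rejection shows only that the rule beats chance. The aim is to defer patients from surgery and downstream testing, so these are very different claims.

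**Working it through.** **Inputs from section 2.4.** N = 39; 6 positives, so 33 negatives (ratio 33/6 = 5.5); alpha 0.05; null AUC A0 = 0.8; stated power 80%; planned enrolment 50. **Not stated, so varied:** the true AUC A1, the sidedness and the variance formula.

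**Formulas.** Hanley-McNeil variance with n1 positives and n0 negatives:

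V(A) = [A(1−A) + (n1−1)(Q1−A²) + (n0−1)(Q2−A²)] / (n1·n0), where Q1 = A/(2−A) and Q2 = 2A²/(1+A).

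With SE0 = √V(A0) and SE1 = √V(A1), power is:
- (a) null plus alternative variance (the standard form): Φ[(A1 − A0 − z·SE0)/SE1]
- (b) alternative variance only: Φ[(A1 − A0)/SE1 − z]
- (c) null variance only: Φ[(A1 − A0)/SE0 − z]

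Here z = 1.96 two-sided or 1.645 one-sided.

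**Step 1: try to reproduce 80% against 0.8.** At A = 0.8, Q1 = 0.8/1.2 = 0.6667 and Q2 = 1.28/1.8 = 0.7111. V = [0.16 + 5 × 0.0267 + 32 × 0.0711]/198 = 2.569/198 = 0.01297, so SE0 = 0.114. The two-sided rejection limit is 0.8 + 1.96 × 0.114 = 1.02, above 1.

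For a true AUC of 0.90, SE1 = 0.087. Two-sided power under (a) is Φ[(0.10 − 0.223)/0.087] = Φ(−1.42) = 8%.

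Power against 0.8 at 6/33:

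| Variant | AUC 0.85 | AUC 0.90 | AUC 0.95 | AUC at which power reaches 80% |
|---|---|---|---|---|
| (a) two-sided | 5% | 8% | 12% | never (maximum 14.6%, near 0.98) |
| (a) one-sided | 9% | 16% | 28% | about 0.998 |
| (b) two-sided | 7% | 21% | 66% | about 0.960 |
| (b) one-sided | 12% | 31% | 76% | about 0.953 |
| (c) two-sided | 6% | 14% | 26% | never |
| (c) one-sided | 11% | 22% | 37% | never |

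The normal approximation is rough with six positives. A binormal simulation with a calibrated critical value gave 19% (upper-tail alpha 0.025) and 28% (0.05) at a true AUC of 0.90. It reached 80% at about 0.98 and 0.97 respectively. The stated figure is not reproduced below about 0.95 by any method tried.

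**Step 2: the planned 50.** At 6/39 = 15.4%, 50 patients give about 8 positives (8/42). At 18% they give 9 (9/41). At a true AUC of 0.90, power is 11-12% two-sided and 20-23% one-sided under (a). The most lenient variant, (b) one-sided, gives 38-41%.

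**Step 3: the size that a null of 0.8 would need.** Under (a) at ratio 5.5, 80% power for 0.90 against 0.80 takes 338 patients two-sided (52/286) or 260 one-sided (40/220).

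**Step 4: what 39 does fit.** Take a null of 0.5 and A1 = 0.85, two-sided, form (a), 6/33. SE0 = 0.130 and SE1 = 0.103, so power = Φ[(0.35 − 0.254)/0.103] = 82%. Five positives give 74%, so 6 + 33 = 39 is the smallest sufficient design at that ratio. Other settings with a null of 0.5 also have 6 + 33 as the smallest design:
- 0.845 to 0.86, two-sided, form (a)
- 0.82 to 0.83, two-sided, form (b)
- 0.82 to 0.83, one-sided, form (a)
- 0.80, one-sided, form (b)

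**The case against.** The strongest reply is that neither an alternative AUC nor the sidedness is stated, so the sentence cannot be called impossible. This stands in part. A reader might infer that 80% power against 0.8 cannot exist at this size, and the article does not support that. Under the alternative-variance form it exists at a true AUC of about 0.953 to 0.960, and at 9/41 that form gives 82.5% two-sided at 0.95. Rejection is ruled out only where the two-sided limit uses the null variance.

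A reader might also infer that the calculation must have been 0.50 against 0.85. It is one candidate among several, no document contains it, and its power at 6/33 is 82%, not 80%. The ratio of 5.5 is itself taken from the stated split. The cited 18% implies a ratio of 82/18 = 4.56, at which 0.5 against 0.85 two-sided gives 6 + 28 = 34. At that ratio, 39 appears as 7 + 32, from about 0.83-0.84 two-sided or 0.80 one-sided.

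Nor does low power make a rejection invalid: if 0.8 is truly tested and rejected, the claim of an AUC above 0.8 is legitimate.

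It could also be said that a fuller document may hold the missing inputs. An expected AUC left to such a document would be no fault. The fault here is that the printed null and the printed power do not fit together at any plausible true AUC, and a fuller document could not make that sentence right.

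**Conclusion.** The concern holds in limited form. As written, the article's only power figure is wrong for any plausible true AUC: against a null of 0.8 at 6/33, power is 5-12% at 0.85 and 8-31% at 0.90, not 80%. Reaching 80% takes near-perfect discrimination, and the standard two-sided calculation never reaches it. The step to 50 patients, justified by uncertain prevalence, does not close the gap.

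These figures rest on the Hanley-McNeil variance, the stated 6/33 split, and 8 to 9 positives among 50. The unstated sidedness and variance form were varied, and no choice changes the conclusion.

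A misdescribed null is the likeliest explanation, since 39 follows readily from a null of 0.5 with an expected AUC of about 0.80-0.86. That is an inference; the article does not show which values were entered. It also does not follow that the trial must recruit 338 patients. That number shows only how far the stated claim lies from the design.

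**What to change.** In section 2.4, state the null AUC, the expected AUC and the sidedness actually entered in the software. These should come from the sponsor's record of the calculation, not from a reconstruction.

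- **If the null was 0.5:** say so, and state that rejection shows discrimination better than chance, not an AUC above 0.8.
- **If 0.8 is the intended benchmark:** keep N = 50 and replace the 80% with recomputed power, naming the true AUC, variance method and number of positives assumed. Report the AUC with its confidence interval. At an AUC of 0.8 with 9/41, SE = 0.093, so the half-width is 1.96 × 0.093 = about 0.18.

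The cost is one corrected passage and no extra patients. The drawback is that either the stated power or the claim it supports becomes less favourable.

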## Conclusion

3

CCTA has emerged as a noninvasive imaging modality, which is widely used to describe anatomic features of AAOCA. Some AAOCA variants are associated with ischemia and adverse cardiac events, whereas most variants may be hemodynamically not relevant and innocent bystanders. It is important to select the optimal patients for further testing and to defer patients who are not at risk for ischemia. However, there is to date no evidence available on how AAOCA patients without risk for ischemia can be ruled out safely based on CCTA-derived anatomy only. The NARCO trial will help to optimize patient selection and risk stratification in order to prevent unnecessary downstream testing and costly interventions in these patients.

## Data sharing statement

The data that support the study findings will be available upon reasonable request.

## Ethical approval information, institution and number(s)

This study design was approved by the Ethics Committee of the Canton of Bern, Switzerland (KEK 2020-00841) and complies with the Declaration of Helsinki.

